**d) Primary Endpoints**

**Safety and Tolerability**:

- Severe local reactogenicity events (pain, tenderness, erythema/skin discoloration, edema, damage [vesiculation/ulceration], induration, formation of a crust or scab.
- Severe systemic reactogenicity events (fever, chills, headache, nausea, vomiting, malaise, myalgia, arthralgia, rash).
- Severe other adverse events (including laboratory abnormalities).
- All Serious Adverse Events.
- Proportion of volunteers with mild and moderate local and systemic reactogenicity events.
- Electroporation Tolerability Assessment Questionnaire Responses (Appendix B)

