No more than one volunteer per day will be enrolled for the first four volunteers to receive electroporation in each dose group. For these four volunteers, an additional telephone call to assess safety and adverse events will be made on the day following vaccination. If four vaccinations by electroporation have occurred without greater than moderate adverse events, the remainder of the group can be enrolled with no fixed interval between volunteers.

A. **Description of Adverse Events (AE) Detection and Reporting:**

**i. Adverse Event Definition**: An adverse event is any noxious, pathologic, or unintended change in anatomical, physiologic, or metabolic functions, as indicated by physical signs, symptoms, and/or laboratory changes occurring in any phase of the clinical trial, whether associated with drug and whether or not considered drug related. All of the following are to be considered adverse events:

- An exacerbation of a pre-existing condition.
- An inter-current illness.
- Any drug interaction.
- Any event related to a concomitant medication.
- Development of an abnormal laboratory value or a significant change from baseline in a laboratory value within the range of normal, considered by the investigator to be clinically important.

Any adverse event prior to the first vaccination will be reported as a pre-existing condition on the “previous conditions” source document. At each outpatient visit, subjects will be questioned and/or examined by the PI or his designee for evidence of AEs. The onset and end dates, severity and relationship to study vaccine and EP device will be recorded in the medical record for each event.

**ii. Assessment of Severity:** The severity of the AE will be assessed according to the Adverse Event Severity Assessment Table (see Appendix C).

**iii. Serious Adverse Event (SAE) Definition:** An SAE is an AE that results in any of the following outcomes.

- Death
- Life threatening condition
- Hospitalization or prolongation of stay
- Persistent or significant disability or incapacity
- Congenital anomaly or birth defect
- Medically significant event, including laboratory abnormalities

Important medical events that do not result in death, are life threatening, or require hospitalization, may be considered SAEs when, based on appropriate medical judgment, they may jeopardize the volunteer, or may require medical/surgical intervention to prevent one of the outcomes listed in this definition.

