**APPENDIX C: ADVERSE EVENT SEVERITY ASSESSMENT TABLE**

| **PARAMETER** | **MILD** | **MODERATE** | | **SEVERE** | |
| --- | --- | --- | --- | --- | --- |
| **General Principle for Severity Assessment** | Mild discomfort. Minimal or no limitation of daily activity.  No need for medical intervention. | Moderate discomfort.  Some limitation of daily activities (e.g. able to work part-time)  May require minimal or no medical intervention | | Severe discomfort. Marked limitation of daily activities (e.g. unable to work). Requires medical intervention. | |
| **LOCAL REACTOGENICITY:** | | |  | |  |
| **Pain and tenderness** | Minimal discomfort associated with minimal or no limitation of use of arm | Moderate discomfort with some limitation of use of arm causing some interference with daily activities. May require single dose of analgesic or NSAID. | | Severe discomfort with significant limitation of use of arm causing marked limitation of daily activities (e.g. unable to work). Requires medical intervention (e.g. repeated doses of analgesic or NSAID). | |
| **Erythema (redness) or skin discoloration** | Light red blush up to 25% of the circumference of the upper arm | Marked redness involving up to 50% of the circumference of the arm | | Brick red involving >50% of the circumference of the upper arm | |
| **Edema (swelling)** | Light edema involving up to 25% of the circumference of the upper arm | Marked edema involving up to 50% of the circumference of the arm | | Significant edema >50% of the circumference of the upper arm | |
| **Induration** | Hardening under the skin <1.5 cm in diameter | Hardening under the skin 1.5-3.0 cm in diameter | | Hardening under the skin >3.0 cm in diameter | |
| **Skin damage (vesicle, ulcer)** | Vesicles or superficial disruption of epithelium < 1 cm | Vesicles or superficial disruption of epithelium 1-2 cm | | Full thickness disruption of the epithelium (ulceration) > 2 cm | |
| **Formation of crust, scab or scar** | Crust, scab or scar = 2cm | Crust, scab or scar 2­4cm | | Crust, scab or scar > 4cm | |

| **SYSTEMIC REACTOGENICITY** | |  |  |
| --- | --- | --- | --- |

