| **Headache** | Minimal headache causing no interference with daily activities | Moderate headache causing some interference with daily activities. May require single dose of analgesic or NSAID. | Significant headache causing marked limitation of daily activities (e.g. unable to work). Requires medical intervention (e.g. repeated doses of analgesic or NSAID). |
| **Rigor (chills)** | Minimal discomfort causing no interference with daily activities | Moderate discomfort causing some interference with daily activities | Significant discomfort causing limitation with daily activities (e.g. unable to work). |
| **Malaise (generalized feeling of discomfort)** | Minimal discomfort causing no interference with daily activities | Moderate discomfort causing some interference with daily activities | Significant discomfort causing limitation with daily activities (e.g. unable to work). |
| **Fatigue (tiredness)** | Minimal discomfort causing no interference with daily activities | Moderate discomfort causing some interference with daily activities | Significant discomfort causing limitation with daily activities (e.g. unable to work). |
| **Myalgia (other than vaccination site)** | Minimal muscle pain causing no interference with daily activities | Moderate muscle pain causing some interference with daily activities. May require single dose of analgesic or NSAID. | Significant muscle pain causing marked limitation of daily activities (e.g. unable to work). Requires medical intervention (e.g. repeated doses of analgesic or NSAID). |
| **Arthralgia** | Minimal joint pain causing no interference with daily activities | Moderate joint pain causing some interference with daily activities. May require single dose of analgesic or NSAID. | Significant joint pain causing marked limitation of daily activities (e.g. unable to work). Requires medical intervention (e.g. repeated doses of analgesic or NSAID). |
| **Fever** | 37.7–38.6°C (99.8– 101.5°F) | 38.7–39.3°C (101.6– 102.7°F) | >39.4°C (>102.8°F) |
| **Nausea** | Minimal nausea causing no interference with daily activities | Moderate nausea causing some interference with daily activities.. | Significant nausea causing marked limitation of daily activities (e.g. unable to work). |

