| **Vomiting** | Minimal nausea causing no interference with daily activities | Moderate nausea causing some interference with daily activities. | Significant nausea causing marked limitation of daily activities (e.g. unable to work). Requires medical intervention |
| --- | --- | --- | --- |
| **Pruritus** | Localized itching at vaccination site | Itching at the injected arm (beyond vaccination site) | Generalized itching |
| **Rash** | Localized maculopapular (non­urticarial) rash at the vaccination site area causing no interference with daily activities | Diffuse maculopapular (non-urticarial) rash at the injected arm (beyond vaccination site) causing some limitation of daily activities | Systemic maculopapular (non­urticarial) rash causing marked limitation of daily activities. Requires medical intervention |
| **Allergic reaction** | Localized urticaria at vaccination site causing no interference with daily activities | Diffuse urticaria at the injected arm (beyond vaccination site) and causing some limitation of daily activities | Systemic urticaria or angioedema causing marked limitation of daily activities. Requires medical intervention |
| **HEMATOLOGY** |  |  |  |
| Hemoglobin | 10.0 g/dL – 11.0 g/dL OR  any decrease = 2.5 g/dL | 9.0 g/dL – 9.9 g/dL OR  any decrease = 3.5 g/dL | = or <8.9 g/dL  OR  any decrease = 4.5 g/dL |
| WBC—Elevated WBC—Decreased | 13,000–14,999/mm3 | 15,000–19,999/mm3 | = or >20,000/mm3 |
| 2000–2499/mm3 | 1500–1999/mm3 | = or <1499/mm3 |
| Absolute Neutrophil Count | 1000–1300/mm3 | 750–999/mm3 | = or <749/mm3 |
| Absolute Lymphocyte Count | 600–649/mm3 | 500–599/mm3 | = or <499/mm3 |
| Absolute CD4 Count (HIV Negative) | 300–400/mm3 | 200–299/mm3 | = or <199/mm3 |
| Platelets—Decreased Platelets—Elevated | 100,000–124,999/mm3 | 50,000–99,999/mm3 | = or <49,999/mm3 |
| NA | 550,000–600,000/mm3 | > 600,000/mm3 |
| **CHEMISTRY** |  |  |  |
| BILIRUBIN (total) | 1.0–1.5 x ULN | >1.5–2.5 x ULN | >2.5 x ULN |
| CREATININE | 1.1–1.3 x ULN | >1.3–1.8 x ULN | >1.8 x ULN |
| AST (SGOT) | 1.51–3.0 x ULN | >3.0–6.0 x ULN | >6.0 x ULN |
| ALT (SGPT) | 1.51–3.0 x ULN | >3.0–6.0 x ULN | >6.0 x ULN |
|  |  |  |  |

| **URINALYSIS** | | |  | |  |
| --- | --- | --- | --- | --- | --- |
| PROTEINURIA | 1+ (30 mg/dL) | 2–3+ (100-500mg/dL) | | 4+ (> 500mg/dL) | |
| Random urine 24-hour urine | 200 mg–500 mg loss/day | > 500 mg–1.0 g loss/day | | > 1.0g loss/day | |

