**APPENDIX D: Volunteer Diary Card**

**Volunteer Diary Card**

**Protocol DHO-0614-0707**

Volunteer ID Number

Date and time of injection

Date of Next Visit:

Name of Study Contact:

24 HOUR EMERGENCY telephone number to report any unusual or severe symptoms that occur before the next visit:

** Please bring this card to your next clinic visit.

If you experience any symptoms following this vaccination that persist beyond day 3 (72 hours) please indicate the severity for each one noted in the column under the day you noticed the symptom. Unless an item says MEASURE, please rate severity as “-“for none, “+” for mild, “++” for moderate, or “+++” for severe.

| **Code** | **Meaning** |
| --- | --- |
| - | Symptom not present |
| + | Mild: Transient or mild discomfort, no limitation in normal daily activity |
| ++ | Moderate: Some limitation in normal daily activity |
| +++ | Severe: Unable to perform normal daily activity |

| **Possible Symptoms** | **Date** | **Date** | **Date** | **Date** | **Date** | **Date** | **Date** |
| --- | --- | --- | --- | --- | --- | --- | --- |
| Local Symptoms  Pain (pain without area being touched) at injection site |  |  |  |  |  |  |  |
| Tenderness (pain when area being touched) at injection site |  |  |  |  |  |  |  |
| Redness (erythema) at injection site  MEASURE | mm | mm | mm | mm | mm | mm | mm |
| Skin damage (vesicles, ulcers) at injection site  MEASURE | mm | mm | mm | mm | mm | mm | mm |
| Hardness or thickening (induration) at injection site MEASURE | mm | mm | mm | mm | mm | mm | mm |
| Swelling (edema) at injection site |  |  |  |  |  |  |  |
| Formation of crust, scab or scar MEASURE | mm | mm | mm | mm | mm | mm | mm |
| Systemic Symptoms  Headache |  |  |  |  |  |  |  |
| Chills |  |  |  |  |  |  |  |
| Nausea |  |  |  |  |  |  |  |
| Vomiting |  |  |  |  |  |  |  |
| Temperature MEASURE  Measure before midnight of the date stated | °F | °F | °F | °F | °F | °F | °F |
| Feeling of general discomfort, uneasiness, a general sick feeling (malaise) |  |  |  |  |  |  |  |
| Muscle aches (myalgia) |  |  |  |  |  |  |  |
| Aching joints (arthralgia) |  |  |  |  |  |  |  |

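### Appendix C governs severity, but the volunteer diary card does not collect what an Appendix C grade needs, so severe reactogenicity between staff contacts may be misgraded in either direction

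*Protocol*

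**What the plan says.** **Endpoint.** Section d) Primary Endpoints lists severe local reactogenicity first and then "Severe systemic reactogenicity events (fever, chills, headache, nausea, vomiting, malaise, myalgia, arthralgia, rash". Neither line names a grading scale.

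**Scale.** The Data and Safety Monitoring Plan, under Assessment of Severity, supplies one: "The severity of the AE will be assessed according to the Adverse Event Severity Assessment Table (see Appendix C". Appendix C has its own local and systemic reactogenicity sections. Its general definition of severe is "Severe discomfort. Marked limitation of daily activities (e.g. unable to work). Requires medical intervention". Its rows for chills, malaise and fatigue use "Significant discomfort causing limitation with daily activities (e.g. unable to work", with no intervention element.

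**Diary card** (headed Appendix D, cited as Appendix E under Vaccination Visits). Volunteers record reactogenicity for a week after each vaccination. Items that are not measured are coded for severity. The moderate code covers some limitation of normal activity, and the next code up is "Severe: Unable to perform normal daily activity". Redness, induration, skin damage and scabs are entered in millimetres. The measuring instructions, which cover thickening, redness and skin damage, round the result to the nearest 10. The systemic rows are headache, chills, nausea, vomiting, temperature, malaise, myalgia and, last, "Aching joints (arthralgia". There is no rash row and no field for analgesic use.

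**Staff contact.** "At each outpatient visit, subjects will be questioned and/or examined by the PI or his designee for evidence of AEs". Post-Vaccination Visits and Appendix A add a telephone call 1 to 4 days after each vaccination, clinic visits starting one week after it, and a review of concomitant medication at those visits.

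**The concern.** Staff must give an Appendix C grade to reactions that may have come and gone before they next see or telephone the volunteer. For those reactions they have the volunteer's recall and the card. If the card's categories and units do not correspond to Appendix C, the grade cannot be read from it, and the protocol states no rule for converting one to the other.

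At stake are the first two primary endpoints in groups of eight. Severity also enters three safety provisions: the release of enrolment after the first four electroporation recipients in each dose group, the removal of volunteers for injection reactions of Grade 3 or above, and the three-volunteer suspension count.

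**Working it through.** The point rests mainly on setting the texts side by side. The protocol gives no figure for this issue.

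**1. Severity wording**

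| Situation | Diary card | Appendix C |
| --- | --- | --- |
| Marked but incomplete limitation, repeated analgesic doses (pain, headache, myalgia, arthralgia) | No matching code; moderate is nearest | Severe |
| Chills or malaise with significant discomfort that limits activity without preventing it | Moderate is nearest | Can be severe; inability to work is only an example |
| Unable to perform normal activity, no medical intervention | Severe | Does not meet the full general definition of severe |

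The first two rows push the grade down if the card is read literally; the third pushes it up. The direction of the net error is not determined.

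**2. Analgesic use.** For pain and tenderness, headache, myalgia and arthralgia, Appendix C uses single against repeated analgesic doses as a marker of moderate against severe. The card does not ask.

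**3. Rash.** The endpoint names nine systemic terms and the card has rows for eight; the missing one is rash. Appendix C grades it, the severe level being systemic "rash causing marked limitation of daily activities. Requires medical intervention".

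**4. Erythema.** Appendix C sets severe at more than 50% of the upper-arm circumference; the card gives the widest extent in millimetres. The protocol gives no arm circumference. Assuming 200 to 400 mm, the cut-off is 0.50 × 200 = 100 mm to 0.50 × 400 = 200 mm. A diary entry of 150 mm would be 150/250 = 60% of a 250 mm arm and 150/350 = 43% of a 350 mm arm, so the extent criterion is met in one and not in the other. The severe level also refers to colour, which the card does not record.

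**5. Induration.** Appendix C: mild below 15 mm, moderate 15 to 30 mm, severe above 30 mm. Rounding to the nearest 10 turns 31, 32, 33 and 34 mm into 30 mm. All four are severe as measured and moderate as recorded.

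**6. Effect of one misgraded volunteer.** Exact two-sided 95% Clopper-Pearson intervals. As a check on the method, the upper bound for 0 of n is 1 − 0.025^(1/n), which gives 0.369, 0.206 and 0.142 for n = 8, 16 and 24. These match the 0.37, 0.21 and 0.14 in Sample Size and Power Calculations, which concern vaccine-related SAEs.

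| Group | None severe | One regraded to severe |
| --- | --- | --- |
| One dose group, n = 8 | 0% (0 to 0.369) | 1/8 = 12.5% (0.003 to 0.527) |
| All ADVAX electroporation recipients, n = 24 | 0% (0 to 0.142) | 1/24 = 4.2% (0.001 to 0.211) |

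**The case against.** The best defence is that the card was never meant to carry the grade. Appendix C is the named scale, the post-vaccination section treats reactogenicity as a kind of adverse event, and nothing makes the diary code the endpoint value. Staff assess reactogenicity at 30 to 45 minutes, by telephone within days and in clinic at about one week, with a further next-day call for the first four electroporation recipients in each dose group. Concomitant medication is reviewed at the post-vaccination visits, so repeated analgesic use may be recovered there. Appendix C's own example of severe, inability to work, is close to the card's wording. Severe rash, as Appendix C defines it, would probably come to light through the calls, the visits or the card's 24-hour number. The analysis is mainly descriptive, and conversion rules may sit in CRF instructions or SOPs that are not shown.

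Much of this stands. A reader might infer that a volunteer's place in the severe endpoint depends on which of two scales is applied. It does not, because the protocol names Appendix C. A reader might also infer that severe events are bound to be under-counted, or that rash drops out of the endpoint. The documents support neither: error can run upward as well, and staff can record a rash whether or not the card has a row for it.

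The defence does not repair the card. Staff contact is intermittent, and questioning cannot restore a measurement already rounded away or turn millimetres into a share of an unmeasured circumference. That Appendix C governs is the reason for the card to match it.

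**Conclusion.** The point holds as a data-capture defect in the diary card. The endpoint's grading scale is not in doubt. Followed as written, the only day-by-day record cannot by itself yield Appendix C grades for several components of a primary endpoint, and reactions that peak and resolve between contacts may be misgraded in either direction.

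The 12.5 points (1/8) is the effect of one misgraded volunteer in a group of eight. It is not an estimate of how often misgrading would occur, and the protocol offers no basis for one. The induration result needs only the protocol's own cut-off and rounding rule. The erythema range rests on the assumed circumference of 200 to 400 mm. The safety provisions run on staff-assessed adverse events, and the suspension count also needs judgements of relatedness and clinical significance, so diary codes reach them only indirectly. No sample-size or precision figure changes. This is a cheap improvement worth making.

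**What to change.** - Print the Appendix C wording for mild, moderate and severe on the card, symptom by symptom where the rows differ.
- Add a rash row and a daily tick box for analgesic use (none, one dose, repeated doses).
- Record measurements to the nearest millimetre, in a form that maps to the Appendix C cut-offs. For erythema, staff could measure upper-arm circumference at the vaccination visit so that the diary extent can be expressed as a share of it.
- State in the Primary Endpoints section that the endpoint grade is the investigator's Appendix C grade, reached from diary entries together with telephone and visit assessments.

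The cost is a reprinted card, a small CRF change and slightly more for volunteers to fill in. The severity scale, the safety rules and the sample size stay as they are.

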5. The application of electroporation will result in a brief, localized muscle contraction at the site of administration, which may be painful. Approximately 10% of subjects may experience a tingling sensation in their arm and fingers after administration. Since intramuscular DNA delivery with electroporation results in increased intracellular uptake of plasmid at the site of injection and electric field application, the procedure may increase the frequency and/or severity of local site reactions. Such symptoms should not last longer than several days. However, volunteers will be removed from the study if injection reactions ≥ Grade 3 in severity occur
6. We do not know what effect the vaccine would have on an unborn child if given to a pregnant woman. Females of childbearing potential will be advised to use a reliable form of contraception, as discussed with a nurse counselor, until study completion. A pregnancy test will be performed at screening, on the day of vaccination, and at every visit throughout the course of the fourteen-month study. Males who are not anatomically sterile (those who have had a vasectomy or medically proven to be sterile)should use condoms until study completion to avoid pregnancy in a spouse or partner
7. Following vaccination a participant may become HIV positive on a routine HIV test. This test result does not mean that person has HIV or AIDS. It could mean that exposure to the vaccine resulted in the production of antibodies to it. In case of a positive HIV test result, an independent laboratory will confirm whether the positive test is the result of the vaccination or whether the participant contracted HIV through exposure in the community. In the event that an individual has a vaccine-induced positive serology, ADARC will provide documentation of that individual’s participation in this vaccine trial
8. It is unknown whether receiving this HIV vaccine will alter the immune response to any future HIV vaccine that may be developed in the future
9. The possibility of integration of the DNA plasmid vector into genomic DNA of transfected myocytes has been considered. Plasmid integration at a sufficiently high frequency carries the possibility of inducing deleterious gene expression modifying mutations (e.g. inactivation of a tumor suppressor gene). Potential side effects could include an increased risk of malignancy arising from the cells harboring the mutation(s).

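### The diary's myalgia row omits Appendix C's exclusion of the vaccination site, so soreness of the injected deltoid can be entered as systemic reactogenicity, plausibly more often with electroporation

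*Protocol*

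**What the plan says.** Three parts of the protocol name the same symptom.

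- **Volunteer Diary Card** (the second of the two appendices lettered D). Under the heading "Systemic Symptoms" there is a row reading "Muscle aches (myalgia", with no restriction on location. Under the local heading there are two separate rows, "Pain (pain without area being touched) at injection site" and "Tenderness (pain when area being touched) at injection site".
- **Appendix C, Adverse Event Severity Assessment Table, systemic reactogenicity.** The graded term is "Myalgia (other than vaccination site". The section on assessment of severity makes this table the standard for grading adverse events.
- **Section d), Primary Endpoints.** The list includes "Severe systemic reactogenicity events (fever, chills, headache, nausea, vomiting, malaise, myalgia, arthralgia, rash" and, at lower grades, "Proportion of volunteers with mild and moderate local and systemic reactogenicity events". Neither item repeats the site limit.

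Risks and Alternative Methods, item 5, describes the device effect: "The application of electroporation will result in a brief, localized muscle contraction at the site of administration, which may be painful". It adds that the procedure could make site reactions more common or more severe, without giving a figure.

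**The concern.** The product goes into the deltoid, and electroporation makes that muscle contract. To a lay volunteer a sore deltoid is a muscle ache. Appendix C foresees this and excludes the vaccination site, but the form the volunteer completes has lost the exclusion. A volunteer can mark injection-site pain and the myalgia row for the same soreness without breaking any instruction on the card, and the card does not record where the ache was.

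At stake is the systemic part of the primary safety endpoint. A local effect counted as systemic would raise the systemic rate. If local muscle effects are more frequent with EP, the rise would be larger there than in the IM arm, and a reader of the tables could not see that from the diary data.

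**Working it through.** The documents give no rate of injection-site muscle soreness by route and no rate of misrecording. The check is therefore a comparison of texts, followed by a look at which contrasts are exposed.

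**1. Definitions side by side**

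| Place | Term | Vaccination site excluded? |
| --- | --- | --- |
| Diary card, systemic rows | "Muscle aches (myalgia" | No |
| Appendix C, systemic rows | "Myalgia (other than vaccination site" | Yes |
| Section d), severe systemic events | myalgia, unqualified | No |

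Only the grading table carries the limit.

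**2. Does another part of the protocol close the gap?**

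- The local rows give deltoid soreness a proper place, but nothing says it belongs only there.
- Under Vaccination Visits, staff explain how to fill in the diary. The content of that explanation is not given, and the site limit is not mentioned.
- Under Post-Vaccination Visits, staff phone 1 to 4 days after each vaccination. Appendix A marks a local and systemic reactogenicity assessment at the D3, D59 and D255 calls. The first four EP recipients in each dose group also get a next-day call. No instruction says to ask where a muscle ache was.
- Grading by Appendix C would remove a deltoid ache from myalgia if staff knew its location. The card does not tell them.

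These steps lower the risk without removing it.

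**3. Which comparisons are exposed?**

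The planned arms are 24 ADVAX/EP, 8 saline/EP and 8 ADVAX IM, so 24 + 8 = 32 volunteers receive EP and 8 receive IM.

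- Absolute systemic rates in the EP arms: exposed.
- EP versus IM: exposed if local soreness differs by route, which the protocol expects but does not quantify.
- ADVAX/EP versus saline/EP: largely protected, because both share the device and its contraction.

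**4. What a size would depend on**

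Let t be the true systemic myalgia rate (equal in both routes), L the rate of injected-muscle soreness, and s the share of sore volunteers who also mark the myalgia row. If these act independently and staff correct nothing:

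- recorded rate = 1 − (1 − t)(1 − L·s)
- spurious EP minus IM difference = (1 − t) · s · (L_EP − L_IM)

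The difference is zero if nobody cross-marks (s = 0) or if soreness is equal by route. None of t, s, L_EP or L_IM is in the documents, so the expression gives a direction but no value.

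**5. Granularity**

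One misrecorded volunteer moves a rate by 1/8 = 12.5 points in the IM arm or in any single EP dose group, by 1/24 = 4.2 points in pooled ADVAX/EP, and by 1/32 = 3.1 points across all EP recipients. This is the step size of the observed rates and says nothing about how many volunteers would be affected.

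**The case against.** The case on the other side is substantial.

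- **The layout steers volunteers correctly.** Pain and tenderness come first, are labelled as at the injection site, and stand under a local heading. The myalgia row sits among general symptoms. A reader might infer that deltoid soreness *will* be recorded as systemic. The documents support only that it *can* be.
- **Staff have early contact.** A reader might infer that the clinic can separate the two only from memory at Weeks 1, 9 or 37. The phone assessments contradict that. Nor can one lean on the background statement that local effects resolved within 48 hours: it concerns a different DNA vaccine given by conventional intramuscular injection.
- **The card's wording may keep early soreness off it.** The card asks for symptoms lasting past day 3. Read literally, that would omit brief soreness. Vaccination Visits, however, asks for Day 1 to Day 7, and the card's own measuring instructions cover Days 1 to 3, so this protection is not dependable.
- **There is a device control.** A reader might infer that a device effect would pass for systemic toxicity of the vaccine. The saline/EP arm would show the same misrecording, so that reading fails.
- **No decision rule turns on it.** The analysis is descriptive, and the protocol concedes little power to compare arms. Suspension depends on serious or severe events that the investigator judges related and clinically significant, not on raw diary entries.

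All of this stands and limits the consequence. None of it supplies the missing site limit or tells anyone to apply it to the diary.

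**Conclusion.** The mismatch is real and visible in the text: the diary row is wider than the protocol's own definition of systemic myalgia, and that symptom belongs to a primary endpoint. Misrecording of deltoid soreness is possible and, if it occurs, plausibly more frequent with EP. The difference by route is an inference from the protocol's description of the device; the documents do not demonstrate it.

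The size cannot be estimated. It is tempting to put assumed values into the formula. With t = 15%, soreness 80% with EP and 40% with IM, and cross-marking of 25% to 75%, it gives 0.85 × 0.25 × 0.40 = 8.5 points up to 0.85 × 0.75 × 0.40 = 25.5 points. Every one of those inputs is invented and correction by staff is set to nil. The result also describes one diary row rather than the endpoint. A volunteer already counted for headache, malaise or another systemic symptom adds nothing to the proportion with systemic events. These figures should not be read as a bias in this trial.

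The point is a wording correction worth making because it costs almost nothing. It does not threaten the trial's conclusions.

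**What to change.** 1. Change the diary row to: *Muscle aches (myalgia) other than at the vaccination site*.
2. Add one line to the card: *Record soreness of the injected muscle under Pain or Tenderness.* Staff should give the same direction when they explain the diary and at the phone assessments.
3. State that myalgia counts in the systemic endpoint only when it meets the Appendix C definition, so that diary, grading table and endpoint list agree.

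The cost is a few words on the card and one sentence on the endpoint. No visit, procedure, volunteer or clinical rule changes. For cards already completed, only the third step can help, and only where the staff record shows where the ache was.
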